### Exclusion criteria

Individuals will be excluded from the Start4All study during both FBCF and CBCF if they cannot provide written informed consent or an agreement to follow up, are undergoing current anti-TB treatment (counting from the third dose), have received any anti-TB treatment or TB preventative therapy within 6 months prior to enrolment (3 months for children), or are exhibiting any clinical ‘danger signs’. Danger signs include but are not limited to respiratory rate >30/min, and/or fever >39°C and/or pulse rate >120/min and/or unable to walk and/or miliary TB found on CXR (i.e., high clinical suspicion of mycobacteraemia and high likelihood of clinical deterioration).

### Participant flow

For individuals recruited via community-based screening, a CXR will be taken prior to study enrolment, supported by the national NTP as routine practice in CBCF activities. For those recruited via facility-based screening, CXR will occur after study enrolment. Individuals who meet the eligibility criteria will then be invited to a private room within the health care facility, provided with a patient information leaflet, and given an opportunity to ask any questions about participation. They will be ensured their decision to agree or decline the invitation will not negatively impact their routine care. Following written informed consent, individuals will be interviewed by the Start4All study team and a comprehensive case report form (CRF) will be taken (Supplementary Material 3). This will include key demographics, TB history – both personal and household – and data on associated TB risk factors. Participants will then be asked to provide two spot sputum samples 30 minutes apart, whole blood, a CXR (for those enrolled via FBCF), and urine. The Figure outlines the specimen collection procedure and testing conducted as part of the study. For children, where sufficient sputum samples cannot be obtained, per national guidelines, one or more of the following specimens will be taken to allow reference standard testing: induced sputum, gastric aspirate, nasopharyngeal aspirate, and stool. In Cameroon, venous whole blood will be used as this is routine clinical practice, but for all other countries capillary whole blood will be used from a single finger prick sample. For all adults, only one PA CXR will be taken. Thus, for individuals recruited through CBCF, the CXR taken during pre-consent eligibility screening will be used for CAD software processing, while those recruited through FBCF, will have their CXR taken and processed with the CAD software following study enrolment. For children aged <10, an additional lateral CXR image will be taken.

**Figure. fig1:**
[figure not shown]
Outline of specimen collection. CRP = C-reactive protein; POC = point of care; CAD = computer-aided detection; MGIT = mycobacteria growth indicator tube.

## TEST METHODS

### Microbiological reference standard (MRS)

The microbiological reference standard in this evaluation will be mycobacteria growth indicator tube culture, for all countries except Brazil, where, as is routine practice, solid culture using Löwenstein–Jensen media will be used. The results of the MRS will not be disclosed to the laboratory personnel performing the experimental test evaluations.

### Routine TB testing

All participants from all countries will have a single sputum Xpert Ultra test performed, with results made available to the clinical team for case management. For children, in addition to culture and Xpert Ultra testing, Cameroon and Viet Nam routinely perform a tuberculin skin test (TST); a Arkay PPD (Japan) and BB-NCIPD (Bulgaria) TB skin test (TST), respectively, results will be recorded but not used as part of reference standard classification. In Bangladesh, Brazil, Cameroon, Kenya, and Malawi, sputum smear microscopy will be performed, at health care facilities as routine practice. The national standard of care and experimental tests introduced as part of this study are outlined in Supplementary Material 4.

### TB case definition

For adults, disease status will be determined through MRS confirmation and will be independent to TB treatment notification, which will not be evaluated in Start4All Phase 1. Children will be classified for the purposes of test evaluation using the ‘updated clinical case definition for classification of intrathoracic tuberculosis in children’.^16^ Where radiological symptoms are to be used for case definition, the corresponding CXRs will be interpreted by a paediatric radiologist from a high-TB-burden country as coordinated by Worldwide Radiology (WWR), an organisation developing radiological capacity in low resource settings. Start4All will not influence the on-site clinical decision making of health care workers related to any participants.

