**METHODS:**

Start4All a multi-country, cross-sectional diagnostic accuracy study (in Bangladesh, Brazil, Cameroon, Kenya, Malawi, Nigeria, and Viet Nam) aims to assess and model algorithms using combinations of WHO-endorsed, and experimental TB screening and diagnostic tests across the lowest levels of care and the community, compared to a sputum culture reference standard. Evaluated tools include C-reactive protein tests, computer-aided detection–interpreted chest X-rays, pooled Xpert® MTB/RIF Ultra (Xpert Ultra) testing, and a third generation lipoarabinomannan (LF-LAM) assay.

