### Experimental test selection

As part of Start4All Phase 1, two classes of WHO-recommended TB screening tests will be evaluated: CRP and CXRs interpreted by CAD software. However, both are restricted to use in specific populations, with CRP limited to PLHIV and CXR with CAD in adolescents and adults aged ≥15 years in place of human interpreters. Concurrently, using the molecular WHO-recommended low complexity nucleic acid amplification test (LC-NAAT) Xpert Ultra, the strategy of pooling sputum samples from multiple individuals and testing with one cartridge will also be investigated, hereby known as pooled testing. In Start4All, this will preferentially be a pool ratio of 4:1, but if an odd number of specimens are collected (e.g., not evenly divisible by four) or sufficient specimens are not available, ratios of 3:1 and 2:1 will be performed. Finally, a new (third) generation LF-LAM assay will be evaluated for diagnostic accuracy across the general population and not just in PLHIV, a population which is not currently recommended for LAM testing by WHO. Supplementary Data S4 describes all experimental tests used as part of this study. Experimental test results will not be shared with the clinical team and so will not influence clinical management. The only exceptions are in Cameroon where pooling of sputum is routinely implemented to optimise cartridge use and in Bangladesh where CAD interpretation of CXRs is being routinely used by the NTP.

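### Adult TB status is fixed as sputum culture alone, so TB that culture misses counts against urine LAM, CRP and CAD even when the routine individual Xpert Ultra is positive

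*Protocol article*

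**What the plan says.** The abstract of the protocol article describes the evaluation as "compared to a sputum culture reference standard". The section on the microbiological reference standard (MRS) defines it as culture only: "The microbiological reference standard in this evaluation will be mycobacteria growth indicator tube culture, for all countries except Brazil", where solid culture is used instead. The TB case definition section applies this to adults: "For adults, disease status will be determined through MRS confirmation and will be independent to TB treatment notification".

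Children are handled differently: "Children will be classified for the purposes of test evaluation using the" published clinical case definition, which is not culture alone.

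Under Routine TB testing, "All participants from all countries will have a single sputum Xpert Ultra test performed". Its stated purpose is case management, and no section shown places it in the adult reference standard.

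On LAM, "a new (third) generation LF-LAM assay will be evaluated for diagnostic accuracy across the general population and not just in PLHIV". The sample is non-sputum: the Participant flow section lists, besides two sputum samples, "whole blood, a CXR (for those enrolled via FBCF), and urine". The introduction says that people living with HIV (PLHIV) often have paucibacillary disease, and the Conclusions present non-sputum tests as a response to the limits of sputum-dependent algorithms.

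**The concern.** One reason for including LAM is that sputum-based testing falls short in some of the target groups. In adults, however, LAM is scored only against a sputum test. If culture misses a person with TB and LAM finds that person, the analysis records a LAM error. The same applies to CRP and to CAD-read chest X-ray.

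For these three index tests a further microbiological result is available that is not part of the index test, namely the individual Xpert Ultra. An adult who is culture-negative, Ultra-positive and LAM-positive is counted against LAM although two tests on different specimens agree.

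The measures affected are specificity and PPV, both listed as reported metrics. Algorithms are to be selected on performance against the reference standard, so a systematic loss in these measures carries into the comparison. The sample size section assumes that half of the adults are PLHIV, one of the groups in which the document itself expects paucibacillary disease.

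**Working it through.** **What follows from the text alone.** Adult status is culture, so a culture-negative adult is in the non-diseased group whatever Ultra shows. A positive LAM in that adult enters the false-positive count. No figure is needed for this step.

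**Inputs for the size**

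- From the document: the planned adult sample is 7,200 + 7,200 = 14,400, with at least 1,096 microbiologically confirmed cases. That is 1,096/14,400 = 7.6%, so 8% is close to the planned average. Table 1 covers prevalences from 1% to 27%.
- Assumed, not in the document: true LAM specificity 98%; LAM sensitivity *s* = 60%, equal in culture-detected and culture-missed TB; culture yield *y* (share of true TB that culture detects) 95%, 90% or 80%; no false-positive cultures.

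**Formulas, per 1,000 adults with C culture-positives**

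- True TB: T = C/y. Missed TB: M = T − C.
- Apparent LAM false positives: F = 0.02 × (1,000 − T) + s × M.
- Apparent specificity = 1 − F/(1,000 − C).
- Apparent PPV = sC/(sC + F). True PPV = sT/(sT + 0.02 × (1,000 − T)).

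**One case in full (8%, yield 90%).** T = 80/0.90 = 88.89 and M = 8.89. F = 0.02 × 911.11 + 0.60 × 8.89 = 18.22 + 5.33 = 23.56. Apparent specificity = 1 − 23.56/920 = 97.44%, a loss of 0.56 points. Of the apparent false positives, 5.33/23.56 = 23% are people with TB.

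**Results**

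| Culture-positive prevalence | Culture yield | Apparent specificity | Loss (points) | Apparent PPV | True PPV |
|---|---|---|---|---|---|
| 2% | 95% | 97.94% | 0.06 | 37% | 39% |
| 2% | 90% | 97.87% | 0.13 | 36% | 40% |
| 2% | 80% | 97.70% | 0.30 | 35% | 43% |
| 8% | 95% | 97.73% | 0.27 | 70% | 73% |
| 8% | 90% | 97.44% | 0.56 | 67% | 75% |
| 8% | 80% | 96.74% | 1.26 | 62% | 77% |
| 15% | 80% | 95.44% | 2.56 | 70% | 87% |

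With LAM sensitivity 40% instead of 60%, the losses at 8% prevalence are 0.17, 0.37 and 0.83 points.

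**Direction with prevalence.** The loss simplifies to M × (s − 0.02)/(1,000 − C). M is proportional to C at a fixed yield, so the loss shrinks as prevalence falls.

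**How much Ultra could recover.** The table shows the full effect of culture misses. If Ultra detects 25% to 50% of culture-missed TB (a further assumption), then at 8% and yield 90%:

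- 25%: F = 18.22 + 0.60 × 6.67 = 22.22 among 917.78 reference-negatives, specificity 97.58%.
- 50%: F = 18.22 + 0.60 × 4.44 = 20.89 among 915.56, specificity 97.72%.

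Against 97.44% with culture alone, the gain is 0.14 to 0.28 points.

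**The case against.** Culture is a coherent primary reference for presumptive pulmonary TB. One common reference keeps tests, algorithms and countries comparable, and adding Ultra would build the index test into the reference for pooled Xpert. All of this stands, and it is why culture should remain primary. The incorporation argument does not reach LAM, CRP or CAD.

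A supplement or an analysis plan that is not shown may already contain an alternative-reference analysis, and the case definition does not rule one out. That is possible. The point is therefore an improvement on a stated rule and does not allege an omission or a contradiction.

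Three stronger readings are tempting, and the documents support none of them:

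- A reader might infer that the artefact matters most when LAM is extended to the general population at low prevalence. In absolute specificity points it is smallest there: 0.13 at 2% against 0.56 at 8%, both at 90% yield.
- A reader might infer that one or two specificity points will remove LAM from the selected algorithms. At 8% a loss above one point appears only at the lowest yield considered, and above two points only in the 15% row. Selection also depends on feasibility, acceptability and cost-efficiency. Algorithms containing Xpert would in any case still be ranked against culture.
- A reader might call LAM specificity against culture a strict lower bound. That needs assumptions about culture false positives, and about LAM positivity in missed TB, that the documents do not give.

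It is also fair to say that adding Ultra answers a complaint about sputum with a second sputum test. It helps only in part.

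**Conclusion.** The point holds in a limited form. The adult rule scores culture-missed TB as a false positive for LAM, CRP and CAD, including cases that the individual Ultra confirms. Apparent specificity and PPV will tend to be too low if culture misses TB.

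The size cannot be derived from the document. Under the assumptions above, the full loss in LAM specificity is about 0.3 to 1.3 points near the planned average prevalence, a few tenths of a point or less at 2%, and larger where prevalence is higher. PPV moves more: at 8% it reads 70%, 67% or 62% where the true values are 73%, 75% or 77%. If LAM is less sensitive in culture-missed TB than in culture-detected TB, the losses are smaller. An Ultra-extended reference would recover only the part that Ultra detects. This is a worthwhile, inexpensive improvement and does not invalidate the primary analysis.

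**What to change.** Keep culture as the primary reference for all tests and algorithms. In addition, pre-specify a secondary adult reference for LAM, CRP, CAD and any algorithm that contains no Xpert:

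- TB if culture or the individual Xpert Ultra is positive; non-TB only if both are negative.
- Trace-only Ultra calls counted once as positive and once as negative.
- People with previous TB shown separately (TB history is already collected).
- Results by HIV status where known, since testing is not routine in Viet Nam or Bangladesh.

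Do not apply it to pooled Xpert or to algorithms containing Xpert. In reporting, say that LAM specificity against culture is probably underestimated if culture misses TB, and do not call it a strict lower bound.

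The cost is some analysis wording and one extra set of tables, with no new samples or tests. There are two downsides to state. False-positive Ultra results would enter the secondary reference as TB and could lower the apparent sensitivity of LAM, CRP and CAD. TB that is negative on both sputum tests would still count against LAM.

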### HIV testing

All individuals will be asked their HIV status on enrolment. A HIV rapid test will be offered to participants in high HIV burden countries (Brazil, Cameroon, Kenya, Malawi, and Nigeria) when their HIV status is unknown or not available in the medical chart, as per national routine practice. In Viet Nam, HIV testing is not routine at any health care centres included as Start4All study sites. In Bangladesh, HIV testing is not routinely performed amongst people with TB nationally. In children <18 months, HIV testing is based on an HIV RNA or DNA nucleic acid amplification test (PCR), following national guidelines. After a positive HIV result, clinical management will follow local guidelines, including counselling and treatment.

### Experimental test selection

As part of Start4All Phase 1, two classes of WHO-recommended TB screening tests will be evaluated: CRP and CXRs interpreted by CAD software. However, both are restricted to use in specific populations, with CRP limited to PLHIV and CXR with CAD in adolescents and adults aged ≥15 years in place of human interpreters. Concurrently, using the molecular WHO-recommended low complexity nucleic acid amplification test (LC-NAAT) Xpert Ultra, the strategy of pooling sputum samples from multiple individuals and testing with one cartridge will also be investigated, hereby known as pooled testing. In Start4All, this will preferentially be a pool ratio of 4:1, but if an odd number of specimens are collected (e.g., not evenly divisible by four) or sufficient specimens are not available, ratios of 3:1 and 2:1 will be performed. Finally, a new (third) generation LF-LAM assay will be evaluated for diagnostic accuracy across the general population and not just in PLHIV, a population which is not currently recommended for LAM testing by WHO. Supplementary Data S4 describes all experimental tests used as part of this study. Experimental test results will not be shared with the clinical team and so will not influence clinical management. The only exceptions are in Cameroon where pooling of sputum is routinely implemented to optimise cartridge use and in Bangladesh where CAD interpretation of CXRs is being routinely used by the NTP.

### Blinding

It is not feasible to blind study staff performing CAD-CXR or CRP, as both tests are conducted in the same room. However, results from CAD-CXR and CRP will not be shared with staff performing Xpert or culture testing, and vice versa. LAM and pooled testing will be carried out by laboratory personnel who are blinded to patient identifiers and, therefore, to all other test results.

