## METHODS

Start4All Phase 1 is a multi-country cross-sectional prospective diagnostic evaluation study of the performance of CRP (rapid diagnostic test and quantitative point of care platforms), CAD-interpreted CXRs, pooled testing of multiple sputum samples with a single Xpert Ultra cartridge, and third generation LF-LAM – individually and as pre-specified diagnostic algorithms. Where a test is not currently part of routine care, the results will not be shared with the clinical team and thus not interfere with routine clinical management.

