### Community-based case finding

In Bangladesh, Cameroon, Nigeria, and Viet Nam, adults will be consecutively recruited through CBCF initiatives. Based on local context, CBCF will be conducted in informal urban settlements in Bangladesh, rural communities in Cameroon, and amongst nomadic and internally displaced populations in Nigeria and urban low-income communities in Viet Nam. The CBCF will be organised through lung health camps. There will be community sensitisation drives before the health camps to invite people to participate in the camp. All individuals who are interested in being evaluated for lung disease attending the camp will be screened upon contact by both W4SS, under the same parameters as in health care facilities, and by CXR. A posterior-anterior (PA) X-ray will be taken from all individuals and interpreted by CAD software (qXR, Qure.ai, Mumbai, India). Any individuals that have a CAD software abnormality score of ≥0.3, living with HIV and/or a household contact will be eligible for study entry irrespective of symptoms. The threshold of ≥0.3 has been selected based on previous work conducted within our study countries for CBCF activities.^15^

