### Data collected using electronic CRFs

Study data will be collected using electronic case report forms (eCRFs) developed in REDCap,^18,19^ a secure, web-based platform designed and maintained by the Global Health Trials Unit (GHTU). The Databases were designed with built-in range checks, branching logic, and required fields to minimise entry errors and ensure completeness. Paper CRFs were available as an option. Of the eight implementing partners, five will use the REDCap databases designed and hosted by GHTU, two will use REDCap databases built and hosted in-country with the support of data dictionaries supplied by GHTU to ensure uniformity in field and variable naming, and country partners will use a locally developed and locally hosted data collection software,^20^ with data being transferred to GHTU for bulk upload into the central REDCap database. Quantitative data will be captured for all enrolled participants, including demographic characteristics, medical history, clinical examination findings, and results from diagnostic tests. Laboratory data, including microbiological reference standard results, will be entered into separate eCRFs. All digital CXR image files will be linked to anonymised study IDs, processed and stored separately from the study data. Data entry will be performed by trained study nurses, community health workers, and laboratory staff at participating sites across Bangladesh, Brazil, Cameroon, Kenya, Malawi, and Viet Nam. Data will be entered in real time where possible. Local study teams will perform routine checks, and the GHTU team will conduct centralised monitoring and data validation. All records will be linked to unique participant identifiers, with personal identifiers stored separately from study data to preserve confidentiality.

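### A shared room does not rule out blinding CRP against CAD: the rapid CRP reading is left unprotected from the CAD score, which may bias rapid-CRP accuracy and rapid CRP–CAD algorithms

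*Protocol article*

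**What the plan says.** Under Blinding, the protocol article gives one reason for leaving CRP and CAD-CXR open to each other: "It is not feasible to blind study staff performing CAD-CXR or CRP, as both tests are conducted in the same room". The same section protects the other comparisons. It states that "results from CAD-CXR and CRP will not be shared with staff performing Xpert or culture testing, and vice versa", and that "LAM and pooled testing will be carried out by laboratory personnel who are blinded to patient identifiers", and hence to all other results.

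The Methods section evaluates CRP in two formats: "CRP (rapid diagnostic test and quantitative point of care platforms". These and the other tests are assessed singly and within pre-specified algorithms. The primary endpoint covers both individual tests and test combinations.

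The order of testing depends on how participants are recruited:

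- **Community case finding.** "A posterior-anterior (PA) X-ray will be taken from all individuals and interpreted by CAD software", and the score helps decide entry: "Any individuals that have a CAD software abnormality score of ≥0.3, living with HIV and/or a household contact will be eligible". Participant flow confirms that this image is taken before consent, so CAD precedes CRP by design.
- **Facilities.** The CXR follows enrolment. Participant flow lists blood before CXR but fixes no reading order.

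On data handling, the section on electronic CRFs says: "All digital CXR image files will be linked to anonymised study IDs, processed and stored separately from the study data".

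**The concern.** The plan treats masking between index tests as worth having for LAM and pooled Xpert, then gives it up for CRP and CAD on grounds of room layout alone. Timing of reading, locked data entry and delayed display of a score can all be controlled within one room.

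An algorithm's sensitivity and specificity depend on how often its component tests are right or wrong together, among people with and without culture-confirmed TB. If a reader resolves a faint rapid-test line in the light of a known CAD score, some of the agreement between the tests comes from the reading and not from disease. It would not recur where rapid CRP is used as a first step without an X-ray. Rapid CRP's own sensitivity and specificity could move as well. These estimates belong to the primary endpoint, and they inform which algorithms go forward to Phase 2.

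**Working it through.** The plan gives no figure for this effect, so there is none to reproduce. The check has two parts.

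**1. Which readings can be influenced, and where**

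| Reading | Open to influence? | Basis |
|---|---|---|
| CAD score | No | Produced by software |
| Quantitative CRP | Little | Platform reading |
| Rapid CRP | Yes, if read by eye | Reading method not stated in the article; assumed |

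In facilities, nothing in Participant flow, Experimental test selection or the data-collection section prevents rapid CRP being recorded before the CAD score is opened. Images are handled apart from the study data, and outside Bangladesh the CAD output does not go to the clinical team. In community camps the score exists before consent, so no reading order can keep it from coming first.

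**2. How far results could move**

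None of these inputs comes from the documents. Assume CRP sensitivity 0.80 and specificity 0.60, CAD sensitivity 0.90 and specificity 0.70, and independent errors given disease status. Let a share *f* of discordant CRP readings switch to agree with CAD, in either direction.

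- Both-positive sensitivity = 0.80 × 0.90 + *f* × 0.20 × 0.90 = 0.720 + 0.18*f*
- Both-positive false-positive rate = 0.40 × 0.30 + *f* × 0.60 × 0.30 = 0.120 + 0.18*f*
- Either-positive sensitivity = 1 − (0.20 × 0.10 + *f* × 0.80 × 0.10) = 0.980 − 0.08*f*
- Either-positive specificity = 0.60 × 0.70 + *f* × 0.40 × 0.70 = 0.420 + 0.28*f*
- CRP alone: sensitivity = 0.80 + *f*(0.18 − 0.08); specificity = 0.60 + *f*(0.28 − 0.18)

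| *f* | CRP alone (sens/spec) | Both positive | Either positive |
|---|---|---|---|
| 0 | 0.800 / 0.600 | 0.720 / 0.880 | 0.980 / 0.420 |
| 5% | 0.805 / 0.605 | 0.729 / 0.871 | 0.976 / 0.434 |
| 10% | 0.810 / 0.610 | 0.738 / 0.862 | 0.972 / 0.448 |
| 20% | 0.820 / 0.620 | 0.756 / 0.844 | 0.964 / 0.476 |

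Across 5–20% switching, the both-positive rule moves by about 1–4 points. The either-positive rule moves by under 2 points in sensitivity and by about 1–6 points in specificity.

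A second set of assumptions lets readings switch one way only, from negative to positive when CAD is positive. Take CRP 0.80/0.65, CAD 0.85/0.75 and switching share *k*:

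- Both-positive sensitivity = 0.85 × (0.80 + 0.20*k*): 0.680, 0.697 and 0.714 at *k* = 0, 10% and 20%
- Both-positive false-positive rate = 0.25 × (0.35 + 0.65*k*): 0.0875, 0.104 and 0.120

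The two versions agree on scale: a few percentage points, if switching happens at these rates at all.

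**The case against.** Several counter-arguments have force.

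- **Exposure in facilities is inferred.** A reader might take the Blinding section to say that CRP readers know the CAD result. It says only that blinding is not feasible, and does not say which result is seen first. Blood is listed before CXR, and separate image handling may already keep the score out of sight. This stands: the finding is absence of protection, not demonstrated exposure.
- **Order is not a general cure.** A reader might infer that sequencing would solve the problem everywhere. It cannot in community camps, where CAD is a pre-consent eligibility step.
- **Not every CRP–CAD algorithm is at risk.** Those using quantitative CRP have little room for this bias. In a sequence that starts with CAD, a user would read CRP knowing the score, so unmasked reading may match intended use. The concern lies mainly with rapid CRP used first or independently.
- **No contradiction about where CAD is used.** Experimental test selection says: "The only exceptions are in Cameroon where pooling of sputum is routinely implemented to optimise cartridge use and in Bangladesh where CAD interpretation" of X-rays is routine. A reader might set this against the CAD entry criterion used in all four community countries. But that sentence concerns sharing results with the clinical team; deciding study entry is a different use.
- **The size is hypothetical.** Accuracies, independence and switching rates are all assumed. The sensitivity shifts are below the tightest precision target in Table 1 (5%). The assumed CAD specificities do not describe community enrolees, some of whom enter because their score is at least 0.3.
- **Detail may sit in supplements.** Reading method and locked entry may be described there. The waiver and its reason, however, are stated in the article and can be judged on it.

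Masking against culture and Xpert is kept in both directions, so this is not reference-standard review bias.

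**Conclusion.** The point holds in a limited form. The stated reason for waiving blinding between CRP and CAD-CXR is inadequate, and no safeguard is described for the one reading that could be swayed. If the rapid test is read by eye, rapid-CRP accuracy and the joint performance of rapid CRP–CAD algorithms may be biased. Quantitative CRP and the CAD score are largely unaffected.

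The true size is unknown. A few percentage points is what the assumed inputs give, not an estimate for this study. The point merits action because combinations are part of the primary endpoint, the facility remedy is simple, and quantitative CRP offers an internal check.

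**What to change.** 1. **Facilities:** replace the statement that blinding is not feasible with an order rule. The rapid CRP result is recorded and locked in the eCRF before the CAD score is opened.
2. **Community case finding:** state that the CAD score necessarily precedes CRP and acknowledge the limitation. A separate rapid-test reader would help, but the article does not describe camp staffing, so this cannot be assumed available.
3. **Both settings:** report rapid-versus-quantitative CRP agreement by CAD result, separately within culture-positive and culture-negative participants. This assumes both CRP formats are run on the same people. Show the direction of disagreement, because raw agreement can also vary with CAD if CRP values lie closer to the cut-off in one group.
4. **If agreement differs by CAD result:** re-estimate the CRP–CAD algorithms with quantitative CRP as a sensitivity analysis.

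The cost is an SOP and eCRF ordering change, a short delay in viewing CAD at facilities (including Bangladesh, where CAD is in routine use), and one extra table. No new tests are needed. If recruitment is too advanced for the order rule, items 3 and 4 can still be done with data already collected.
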